#### Secondary outcomes

The secondary outcomes are: (1) infant’s first feed, (2) exclusive breastfeeding to 4 months postpartum, (3) exclusive breastfeeding to 6 months postpartum, (4) rate of early introduction of complementary feeding before 4 months, and (5) any breastfeeding duration within 6 months postpartum. The definition of any breastfeeding is “The child has received breastmilk (direct from the breast or expressed) with or without other drink, formula or other infant food” [30].

### Blinding

Study coordinators, participants, nurses conducting the interview and statistician performing the data analysis will be masked to the group allocation. Only the investigator who created the randomisation tables is aware of the randomisation assignments.

### Process evaluation

Several components of the program, including its quality, completeness, exposure and satisfaction, participation rate, recruitment, and content, will be evaluated midway of the intervention. Participants’ perceptions of the readability, usefulness, suitability and relevance of the intervention resources will be collected using a brief questionnaire.

### Exit interview

We will randomly select 10 intervention and 10 control participants (10 program completers and 10 non-completers) to participate in the exit interview. The main purpose is to collect information on participants’ opinions of the intervention program and of the messages they obtain in order to further refine and improve the intervention in future. Reasons for withdrawal before completing the project will be solicited from the non-completers. Each interview will take less than 20 min.

### Sample size

Exclusive breastfeeding rates at 6 months postpartum (the primary outcome variable) and the sample size of the study was determined using the formula as follows [33]:$${\text{n}} = \left\{ {\frac{{{\text{Z}}_{{\alpha /2}} \sqrt {{\text{P}}_{{\text{e}}} \left( {1 - {\text{P}}_{{\text{e}}} } \right)} + {\text{Z}}_{{\beta /2}} \sqrt {{\text{P}}_{1} \left( {1 - {\text{P}}_{1} } \right) + {\text{P}}_{2} (1 - {\text{P}}_{2} )} }}{{{\text{P}}_{1} - {\text{P}}_{2} }}} \right\}^{2}$$

where n is the required sample size for each group; Z_α/2_ and Z_β/2_ are the critical Z values for a given alpha and beta level respectively; P_1_ and P_2_ are the estimated exclusive breastfeeding rates at 6 months in the control and intervention group, respectively; P_e_ = P_1_ × 0.50 + P_2_ × 0.50.

Based on the results of our recent prospective cohort conducted in Chengdu [34], we assume that the exclusive breastfeeding rate for mothers in the control group is P_1_ = 25% at 6 months. In addition, we hypothesize a conservative effect size of 10% improvement in the exclusive breastfeeding rate for the intervention group relative to the control group (P_2_ = 35%). The estimated sample size is 890 (450 per group) under a power of 90% and a two-sided significance level of 5%. Taking into account a loss to follow-up of 10%, the total sample size required at baseline for the RCT is 1000 (500 per group). It was assumed that approximately 20% of women will decline to participate, especially due to the COVID-19 pandemic, we therefore plan to approach about 1250 women at the four hospital antenatal clinics.

### Statistical analysis

Descriptive statistics will be performed to summarise participants’ baseline characteristics and the outcome variables. Independent t-tests or Mann–Whitney U tests will be performed to compare continuous variables and chi-square or Fisher’s exact tests to compare categorical characteristics.

Kaplan–Meier curves and log-rank test will be used to compare breastfeeding duration between the intervention and control groups. The Cox proportion hazards model will be conducted to determine the hazard ratios of exclusive and any breastfeeding cessation, accounting for baseline characteristics and other plausible factors associated with breastfeeding practices. Similar analyses will be applied to analyse the data of complementary foods introduction. Multilevel mixed regression models will be used to assess the effectiveness of intervention program on breastfeeding rates at four and 6 months.

We will follow the intention-to-treat principle with all randomised participants included in the analysis, and the missing data will be imputed based on the best-case and worst-case scenarios. Subgroup analyses will be conducted according to variables of interest.

QSR International NVivo 11 software will be used to perform qualitative analysis. The focus group discussions and in-depth interviews will be transcribed verbatim and inductive thematic analysis will be applied to analysis of the transcripts from process evaluation and the exit interviews.

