**Methods:**

A two-arm, parallel, multicentre randomised controlled trial of 1000 pregnant women will be conducted at four maternity hospitals of Chengdu, China. Eligible women who consent to participate in the trial will be recruited at 28–30 weeks of gestation, and randomly allocated to either the intervention group (participants receive breastfeeding-related information from WeChat) or the control group (participants receive non-breastfeeding information from WeChat) using a central randomisation system on a 1:1 ratio at each participating site. The primary outcomes are exclusive breastfeeding rate and full breastfeeding rate at 6 months postpartum. All randomised participants will be included in the outcome analyses with missing data being imputed based on the best-case and worst-case scenarios. Multilevel mixed regression models will be used in the primary analyses to assess the effectiveness of intervention program on the breastfeeding rates.

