#### Primary outcomes

The primary outcomes are exclusive breastfeeding rate and full breastfeeding rate at 6 months postpartum. We follow the WHO’s definition of exclusive breastfeeding as “Breastfeeding while giving no other food or liquid, not even water, with the exception of drops or syrups consisting of vitamins, mineral supplements or medicines” [30]. Full breastfeeding is defined as “Infants who are receiving almost all of their nutrients from breast milk but take some other liquids such as water, water-based drinks, oral rehydration solutions, ritual fluids, and drops or syrups” [31].

To obtain information on infant feeding practices at 6 months, mothers will be asked the following two questions: (1) How did you feed your baby in the past 24 h? The response options are: “Breastfeeding only”, “Breastfeeding + water/glucose water/fruit juice”, “Mainly breastfeeding but ‘topping up’ with infant formula”, “Mainly infant formula but also breastfeeding”, and “Infant formula only”; (2) Did you give complementary foods to your baby in the past 24 h? If the response is ‘Yes’, mothers will be asked to provide the name of each complementary food. In our study, complementary feeding is defined as feeding infants with solid foods and liquids other than breastmilk or infant formula [32].

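### Best-case and worst-case imputation is the only missing-data rule stated for the outcome analyses; on its usual meaning, neither scenario has the planned power or error rate

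*Protocol article*

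**What the plan says.** The Statistical analysis section of the protocol article states "We will follow the intention-to-treat principle with all randomised participants included in the analysis", and in the same sentence "the missing data will be imputed based on the best-case and worst-case scenarios". The Methods part of the Abstract ties the rule to the outcomes: "All randomised participants will be included in the outcome analyses with missing data being imputed based on the best-case and worst-case scenarios". The sentence after that reads "Multilevel mixed regression models will be used in the primary analyses to assess the effectiveness of intervention program on the breastfeeding rates". The endpoints concerned are binary: "The primary outcomes are exclusive breastfeeding rate and full breastfeeding rate at 6 months postpartum".

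Neither place says what the two scenarios are, calls them sensitivity analyses, offers another way to handle missing outcomes, or says which of the two results is the trial's answer.

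The Sample size section gives the planning figures. For the control group, "we assume that the exclusive breastfeeding rate for mothers in the control group is P_1_ = 25% at 6 months"; for the intervention group it takes 35%. Power is 90% at a two-sided 5% level. It arrives at 450 per group and raises this to 500 per group for 10% loss to follow-up.

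The plan also collects information that could inform a missing 6-month outcome: feeding practice at discharge, 1 month and 4 months (Follow-up and outcomes), and baseline characteristics with an infant-feeding attitude score (Randomisation and baseline data collection).

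**The concern.** Best-case and worst-case imputation is a bounding device. It gives two extreme answers and no central estimate, and it treats each filled-in value as if it had been observed. When the assumed loss is as large as the effect sought (10% and 10 points here), the bounds can be wide enough to swamp that effect. If either bound serves as the test of the intervention, its power and false-positive rate are not those on which the trial was sized.

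The scenarios also ignore what is already known about a woman. One who reported formula feeding only at 4 months and was then lost would be counted as exclusively breastfeeding in one of the two scenarios.

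At stake is the main conclusion on the 6-month rates. The planned Kaplan–Meier and Cox analyses can deal with loss by censoring, but they address duration and cessation, not these rates.

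**Working it through.** **Inputs (Sample size section).** Control rate 25%, intervention rate 35%, two-sided 5% level, 90% power, 10% loss, 500 randomised per arm. Assumptions of this check: loss is equal in both arms (50 women each), the observed women have the planned rates, a pooled two-proportion z-test is used, and hospital clustering is ignored. Only exclusive breastfeeding is covered, because the plan gives no planning rates for full breastfeeding.

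**1. The plan's own figure.** The standard formula is n = {z_α/2·√[2p̄(1−p̄)] + z_β·√[p1(1−p1) + p2(1−p2)]}² / (p1−p2)², with p̄ = 0.30.
- n = {1.960·√0.42 + 1.282·√0.415}² / 0.10² ≈ 440 per arm, close to the stated 450.
- Inflation for loss: 450 / 0.90 = 500.
- Power with 450 observed per arm: Φ[(0.10·√450 − 1.960·√0.42) / √0.415] = Φ(1.32) = 90.7%.

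**2. Opposite imputation, planned effect true.** With equal loss m and observed difference d, the best case is d(1−m) + m and the worst case is d(1−m) − m. They lie 2m apart.
- Best: control 0.9 × 25% = 22.5%; intervention 0.9 × 35% + 10% = 41.5%; difference +19.0 points (95% CI 13.3 to 24.7).
- Worst: control 0.9 × 25% + 10% = 32.5%; intervention 0.9 × 35% = 31.5%; difference −1.0 point (95% CI −6.8 to 4.8), p = 0.73.
- Observed data alone: +10.0 points (95% CI 4.1 to 16.0), p = 0.001.
- The scenarios are 20 points apart, twice the effect sought.

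**3. Rejection rates.** These come from 200,000 simulated trials per setting.

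| Loss per arm | Worst case: significant benefit if 25% vs 35% | Best case: significant benefit if 25% vs 25% |
|---|---|---|
| 2% | 77% | 10% |
| 5% | 33% | 43% |
| 10% | 0.6% | 96% |

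At 10% loss and no effect, the worst case is significant against the intervention in about 96% of trials. A hand check of the 96%: the completed-data standard error is √(0.275 × 0.725 × 2/500) = 0.0282, so significance needs a difference of 1.96 × 0.0282 = 0.0554. The expected difference is 0.10, and its true standard deviation is √(2 × 450 × 0.1875)/500 = 0.0260. Then Φ[(0.10 − 0.0554)/0.0260] = Φ(1.72) ≈ 96%.

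**4. Same-direction imputation.** If each scenario fills both arms alike:
- All missing counted as not breastfeeding: 22.5% vs 31.5%, +9.0 points, p = 0.001, power about 90%.
- All missing counted as breastfeeding: 32.5% vs 41.5%, +9.0 points, p = 0.003, power about 87%.
- Under no effect and equal loss, two-sided error is about 4.6% and 2.5%, so it is not inflated.

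**5. Where the severe result stops.**
- The worst-case difference is negative only when m exceeds 0.10/1.10 = 9.1%. At 5% loss it is 0.95 × 10 − 5 = +4.5 points (p = 0.12).
- At 10% loss, observed rates of 25% vs 43% give a worst case of 32.5% vs 38.7%, +6.2 points, p = 0.04.

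**The case against.** The strongest reply is that the article never defines the two scenarios, that defining them and naming the deciding estimate are commonly left to a statistical analysis plan, and that such a plan may exist. The missing definition alone would indeed be no finding. But the article does more than stay silent: it states in two places that missing data are imputed this way, and the Abstract attaches this to the outcome analyses. A stated rule can be judged as stated. What stands from the reply is that every severe figure is conditional on opposite imputation; step 4 shows a mild result otherwise.

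Several stronger readings are tempting, and the documents do not support them:
- *The imputation rule, not the data, sets the answer.* This is close to true only near the planned effect and loss. An observed difference of about 18 points would survive the worst case, and the 10% loss is a planning allowance.
- *The trial has a 96% false-positive rate.* That would need one scenario alone to be the deciding test, and nothing says so. Read as a pair under no effect, the scenarios give an inconclusive range.
- *Stillbirths and infant deaths will be imputed as exclusively breastfed.* Women are randomised before birth, so the analysis set can contain such cases, but no section says they count as missing outcomes.
- *Earlier feeding status largely predicts the 6-month outcome.* No section says or quantifies this. It is a reason to use those data, not an established figure.
- *Analysing 500 per arm after sizing on 450 is a further error.* Inflating for loss is ordinary planning.

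**Conclusion.** The point holds in a conditional form. The article fixes best-case and worst-case imputation as its only stated handling of missing outcomes, with no central estimate and no deciding rule. On the usual meaning of those terms, and with the plan's own rates and loss, neither scenario delivers the stated 90% power with a 5% error rate: the best case loses control of error, and the worst case loses almost all power. Halving the loss to 5% does not cure it. The planned number of observed outcomes would have met both targets. On the same-direction reading, power stays near plan and error is not inflated, but two results and no deciding rule remain. The conclusion rests on opposite imputation, equal loss in both arms, observed women having the planned rates, and no allowance for hospital clustering.

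**What to change.** - Make a missing-at-random analysis primary. One option is the multilevel model already planned, fitted to observed data. The other is multiple imputation of 6-month status by arm, using hospital, baseline variables including the feeding-attitude score, and feeding status at discharge, 1 month and 4 months. Multiple imputation keeps all randomised women in the analysis.
- Define the best-case and worst-case scenarios, saying how each arm is filled, and keep them as named sensitivity bounds that do not decide the trial.
- State that stillbirth and infant death are not treated as loss to follow-up to be imputed, and how such cases enter the analysis.
- Settle this before allocation is unmasked for analysis.

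The cost is wording and a little extra analysis; no new data are needed. The downside is reliance on the missing-at-random assumption, which the bounds then test.

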### Monitoring

We will develop a data monitoring committee (DMC) to monitor conduct and quality of the trial. The DMC includes four independent members with expertise in maternal and infant health, nutrition, biostatistics and trial methodology. The DMC meeting will take place every 6 months.

## Discussion

Although breastfeeding is widely recognized as the best feeding method for infants, the breastfeeding practices in China, in particular exclusive breastfeeding, remain resistant to improvement. The present trial is designed to improve breastfeeding practices of mothers who have a smartphone in urban China. It will be the first study to evaluate the effectiveness of delivering a breastfeeding intervention via WeChat for Chinese mothers.

One main strength of our proposed trial is the use of the widely available and highly convenient tool—WeChat. Every day, more than one billon WeChat users open WeChat at least once, 45 billion messages are sent, and 410 million audio and video calls are made [35]. WeChat is now the most popular social media platform among Chinese. According to our previous research, many mothers in China still have misconceptions on infant feeding and lack true understanding of the health benefits of breastfeeding, both of which largely contribute to the introduction of infant formula within 6 months in China [36]. Delivery of evidence-based educational messages using modern smartphone technology and popular social media networks has the potential to empower mothers to make better informed decisions regarding infant feeding. In addition, the adoption of an RCT design confers a sound basis and an ideal condition for evaluating the intervention effectiveness.

Our study has some limitations. Since we do not have access to the login information of WeChat users, the data on participants’ actual exposure to and uptake of the educational messages will not be available. However, during follow-up, we will ask the mothers to report whether and how often they actually log on WeChat to read the educational messages. In addition, we only follow up mothers to 6 months postpartum due to budget constraint. A longer term of follow-up of 1 year or more is recommended in future studies.

Exclusive breastfeeding provides the most cost-effective intervention for improving the health of infants in the short term and later in life. This trial will use the most widely used social media program as a means of delivering messages to mothers to increase exclusive breastfeeding. Increasing exclusive breastfeeding will contribute to meeting the health and environmental goals of the Sustainable Development Guidelines.

## Data Availability

The datasets used and/or analysed during the current study are available from the corresponding author on reasonable request.

## Abbreviations

COVID-19: Coronavirus disease 2019
DMC: Data monitoring committee
QR: Quick response
RCT: Randomised controlled trial
SMS: Short messages service
WHO: World Health Organization
